#### Mediation Analyses

Mediation effects of therapeutic alliance and adherence to the intervention will be analyzed in a 1-1-1 multilevel mediation model with all variables measured at assessment time points (ie, baseline, midintervention, and post intervention), and all causal paths allowed to vary between participants.

Mediation effects of mechanisms of change in social anxiety will be explored in 2 different lower-level mediation analyses using multilevel modeling. In a 2-1-1 mediation analysis, time will be included as a fixed effect, baseline social anxiety as a level-2 fixed effect predictor, mechanisms of change (ie, automatic thoughts, avoidance, self-focused attention, pre-event, and postevent processing) as a level-1 random effect mediator, and momentary social anxiety as a level-1 random effect outcome. In a 1-1-1 mediation analysis, all constructs will be assessed at level-1. Thereby, social anxiety as a random effect predictor will be assessed concurrent with the random effect mediator, mechanisms of change in social anxiety, and the random effect outcome social anxiety will be assessed 1 prompt later (lead analysis).

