The primary objective of this study is to examine the efficacy of an online intervention called SOPHIE for adolescents with subclinical social anxiety or SAD compared to a care-as-usual (CAU) control group. Thereby, the name SOPHIE is derived from the German term “SOziale PHobIE” (social phobia). It is hypothesized that SOPHIE will be superior to CAU in reducing social anxiety symptoms post assessment and that the intervention effect will be maintained until follow-up assessment 3 months after intervention completion. Furthermore, it is hypothesized that SOPHIE will also have beneficial effects on secondary outcomes, such as depressive as well as general anxiety symptoms, level of functioning, self-esteem, and quality of life at post assessment and follow-up. It is further hypothesized that intervention effects will be moderated by therapeutic alliance, adherence, treatment motivation, and treatment expectation of the online intervention. Moreover, by measuring social anxiety symptoms in their natural context longitudinally, we will examine if intervention effects translate into everyday life and if the postulated maintaining factors of SAD function as mediators of change. Additionally, we intend to model the network structure of social anxiety symptoms at each time point and observe differences in networks of adolescents (eg, regarding age, gender, and severity of social anxiety).

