	Self-esteem	The *Rosenberg Self-Esteem Scale* [84] assesses self-esteem in 10 items on a Guttman scale. This questionnaire is applicable to different age groups; in this study, the adolescent version is applied.	✓		✓		✓	✓
	Therapy expectancy	The *Credibility or Expectancy Questionnaire* [85] assesses treatment expectancy and credibility with 6 items. There are 2 rating scales, 1 from *not at all* (1) to *very* (9) and another from 0 to 100%. For this study, the wording of the items was adapted to the target group of adolescents.	✓					
	Therapy motivation	The *Motivation for Youth’s Treatment Scale* (MYTS) [86] measures adolescent’s motivation for therapy through a self-report questionnaire. Eight items are rated on a 5-point Likert scale from strongly disagree (1) to strongly agree (5). All adolescents complete this assessment at baseline, only adolescents randomized to the intervention group complete the MYTS at week 2, 4, 6, and 8.	✓	(✓)^b^	(✓)	(✓)	(✓)	
	Negative effects of intervention	The *Inventory for assessment of negative effects in psychotherapy* (German: Inventar zur Erfassung Negativer Effekte in der Psychotherapy, Kinder-INEP; [87,88]) has been adjusted to the online format of the intervention, reducing the questionnaire by 6 items to 15 items. This questionnaire is only answered by adolescents in the intervention group.					(✓)	
	Satisfaction with the intervention	The *ZUF-8* is an 8-item questionnaire for global, unidimensional assessment of patient satisfaction [89]. The questionnaire was adapted accordingly to measure satisfaction with the online intervention. Adolescents randomized to the intervention answer questions on a 4-point Likert scale from 1 to 4.					(✓)	
	Therapeutic alliance	The *Working Alliance Inventory for guided Internet Interventions* (WAI-I; [90]) is a self-report questionnaire that measures therapeutic alliance in online interventions with therapeutic support. The 12 items rated on a 5-point Likert scale from *rarely* (1) to *always* (5) were adapted to adolescents. Only adolescents in the intervention group are assessed with the WAI-I.		✓	✓	✓	✓	

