	Adherence to the online intervention	Adherence is operationalized through the extent to which the online intervention is used. The number of finished modules, the number of completed exercises, and the time spent in the online intervention are recorded automatically. As in other studies of online interventions, adherence is calculated with respect to each of these variables and with respect to a composite measure [91].					(✓)	

^a^SAD: social anxiety disorder.

^b^Indicated time points in parentheses reflect assessments only administered in the intervention group.

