#### Care-as-Usual Group

Participants randomized to the CAU group are only contacted for assessments and receive access to the online intervention after follow-up. They are free to take advantage of any other health service. To account for additional help, the use of assistance is assessed post intervention and follow-up (details in Table 1).

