#### Further Analyses

Secondary outcomes (ie, global functioning, general anxiety symptoms, depressive symptoms, quality of life, self-esteem, and guardians’ rating of their child’s social anxiety) will be analyzed using Linear Mixed Effects Model as described earlier. In further analyses, therapy expectancy, therapy motivation (both adolescents’ and guardians’), and satisfaction with the intervention will be added as moderators. Categorical outcomes (eg, diagnostic status) will be analyzed using General Linear Mixed Effect Models with intervention condition, diagnostic status, and time course as fixed effects and participants as random effect. Additionally, Growth Mixture Modeling will be used to identify subpopulations with comparable growth trajectories of social anxiety and secondary outcomes over time (latent classes) and to identify predictors of these classes.

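### Alliance, adherence and satisfaction arise only after randomisation and only in the SOPHIE arm, so they cannot moderate or mediate the SOPHIE-versus-CAU effect, and the alliance/adherence mediation model names a baseline measurement that Table 1 does not contain

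*Protocol article*

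**What the plan says.** **Mediation model.** In the Protocol article, Plan of Analysis, Mediation Analyses, alliance and adherence enter a 1-1-1 multilevel mediation model with "all variables measured at assessment time points (ie, baseline, midintervention, and post intervention"). All causal paths may vary between participants. The section does not name the predictor or say which arm or arms are analysed.

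**Measurement (Table 1).**
- Alliance is ticked at weeks 2, 4, 6 and 8, not at baseline, and the row states: "Only adolescents in the intervention group are assessed with the WAI-I".
- On adherence: "Adherence is operationalized through the extent to which the online intervention is used". It has one tick, at week 8, in parentheses. The footnote explains: "Indicated time points in parentheses reflect assessments only administered in the intervention group".
- Satisfaction has one tick, at week 8, also in parentheses: "Adolescents randomized to the intervention answer questions on a 4-point Likert scale from 1 to 4".

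**Control arm.** Under Care-as-Usual Group, CAU participants "receive access to the online intervention after follow-up".

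**Moderators.** Further Analyses states that expectancy, motivation (adolescents' and guardians') and "satisfaction with the intervention will be added as moderators".

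**Hypothesis.** The last paragraph of the Introduction expects that "intervention effects will be moderated by therapeutic alliance, adherence, treatment motivation, and treatment expectation of the online intervention". The Abstract (Methods) instead lists motivation, expectancy and satisfaction as potential moderators, and alliance and adherence as potential mediators.

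**The concern.** A moderator of a treatment effect needs values in both arms, preferably from before randomisation. A mediator of the arm effect needs a mediator-outcome relation that is not drawn from one arm alone. Alliance with an e-coach, use of the program and satisfaction with it have no counterpart in CAU during the trial. Satisfaction is also measured at week 8, together with the post-intervention outcome, so it may be a result of improvement rather than a condition for it.

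Moderators and mediators are part of the trial's stated objective. If the models are run as written, the software may drop CAU or alias a term. A correlation within the SOPHIE arm (adolescents who improve report better alliance and higher satisfaction) could then be read as moderation or mediation of efficacy. Calling the same two variables moderators in one place and mediators in others also leaves unclear which hypothesis is tested.

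**Working it through.** **1. Size of the arms.** The stated sample size reproduces. Inputs from Sample Size: d = 0.35 (SAD) and 0.20 (subclinical), α = 5%, power 80%, r = 0.4. Study Design gives m = 4 occasions. Assumed here: repeated-measures ANOVA, within-between interaction, two groups, f = d/2, sphericity. The noncentrality is λ = N f² m / (1 − r), with 3 and 3(N − 2) degrees of freedom.
- SAD: λ = 56 × 0.175² × 4 / 0.6 = 11.43; power 0.810.
- Subclinical: λ = 166 × 0.10² × 4 / 0.6 = 11.07; power 0.803.

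The total is 56 + 166 = 222. With 1:1 allocation each arm has 28 + 83 = 111. Only this arm size is used below.

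**2. What the model asks for and what Table 1 holds.**

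| Variable | Arm | Baseline | Week 4 | Week 8 |
|---|---|---|---|---|
| Alliance | SOPHIE only | no | yes | yes |
| Adherence | SOPHIE only | no | not ticked; automatic log may supply it | yes |
| Satisfaction | SOPHIE only | no | no | yes |
| Expectancy | both | yes | no | no |
| Motivation | both at baseline, SOPHIE only later | yes | SOPHIE | SOPHIE |

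Of the three occasions named for the mediation model, alliance has two. Adherence has one in the table, or two if the log is used.

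**3. Can an arm-by-variable term be estimated?** Let A be condition (1 = SOPHIE, 0 = CAU). The design columns are 1, A, the variable, and A × variable.
- Satisfaction S, missing in CAU: complete cases are the 111 SOPHIE participants. There A = 1 throughout, so A equals the constant and A × S equals S. Rank 2 of 4: neither the arm effect nor the interaction can be estimated.
- Adherence M, set to 0 in CAU: A × M equals M for everyone. Rank 3 of 4: there is no separate moderation term. Without the interaction, the columns 1, A, M have rank 3 of 3, so a fit is returned. But M is constant in CAU, so its coefficient comes only from non-randomised variation within SOPHIE.
- Alliance is missing in CAU, so it behaves like satisfaction.
- Baseline expectancy or motivation, both arms: rank 4 of 4, so moderation can be estimated.
- SOPHIE arm alone, with constant, time and alliance at weeks 4 and 8: rank 3 of 3. A process association can be estimated, but it contains no arm contrast.

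**4. Paths that vary between participants, with two occasions.** Suppose the level-1 predictor is time. Two fixed occasions give a 2 × 2 outcome covariance matrix with 3 distinct elements. A random intercept, a random slope, their covariance and a residual variance make 4 parameters, so the model is not identified (rank 3 of 4). Adding a random slope for a mediator that differs between people gives 7 parameters: 6 for the 3 × 3 covariance matrix and 1 residual. The rank is then 6 of 7. If the predictor is instead continuous and differs between people, the ranks are 4 of 4 and 7 of 7. The model is then formally identified but rests on two occasions per person.

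**The case against.** The strongest defence has four parts.

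*Most of the moderator analysis is sound.* This stands. Expectancy and adolescent motivation are collected at baseline in both arms, and guardians' ratings at baseline are not restricted by arm. A reader might infer that the whole moderator analysis is uninformative about SOPHIE versus CAU. The documents do not support that: in Further Analyses only satisfaction fails.

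*The mediator aim in the Introduction concerns the maintaining factors of social anxiety.* This also stands. That aim is served by the EMA models in the second paragraph of Mediation Analyses. All participants provide EMA data, and those models do not use alliance, adherence or satisfaction.

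*The article never says that condition is the predictor of the 1-1-1 model.* True. Condition is constant within a person, and one might infer that it has been misplaced at level 1. But no predictor is named, and an article may leave that to a fuller document. A within-SOPHIE reading can be estimated. What remains is that the model is not labelled as within-arm and that its stated baseline occasion contradicts Table 1.

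*Adherence is logged automatically, and the random paths are not always unidentified.* Both are fair. A week-4 value for use may be recoverable, so the single tick should not be read as proof that only one record exists. Non-identification holds if time is the predictor, not in general.

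None of this rescues satisfaction as a moderator, the hypothesis of moderation by alliance and adherence, or the baseline occasion.

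**Conclusion.** The plan is wrong as written on three linked points, all in secondary analyses:

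1. Satisfaction cannot moderate the SOPHIE-versus-CAU effect.
2. The Introduction's hypothesis that alliance and adherence moderate that effect cannot be estimated, and it conflicts with their role as mediators in the Abstract and Mediation Analyses. As mediators they inform only a within-SOPHIE relation.
3. The 1-1-1 model requires a baseline occasion that does not exist for either variable. With at most two of the three named occasions usable for alliance, letting every path vary between participants is weakly supported, and with time as predictor it is not identified.

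The size is structural: about 111 of 222 participants carry no information on these relations, however complete follow-up is. This assumes full recruitment and equal arms, but the rank results do not depend on the exact number.

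A reader might infer that the trial's efficacy result is compromised. It is not. The primary model uses none of these variables, and the sample size reproduces.

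**What to change.** - **Moderators of the arm effect:** limit them to baseline expectancy and baseline motivation (adolescent and guardian), entered as condition × moderator terms. Do not use the motivation scores from weeks 2 to 8, which exist only in SOPHIE.
- **Satisfaction:** remove it as a moderator and report it descriptively in the SOPHIE arm.
- **Alliance and adherence:** restate the model as an exploratory SOPHIE-arm process analysis without a baseline occasion. Let earlier alliance (weeks 2 or 4) and logged use up to week 4 predict later SPIN, adjusted for earlier SPIN, with fixed slopes. Label the result as association. First confirm that the log can be cut at week 4.
- **Wording:** reconcile the Introduction hypothesis with the Abstract, Further Analyses and Mediation Analyses, so that each variable has one role.
- **Optional:** a complier-average analysis of adherence using randomisation. It would need a stated exclusion restriction and is not required to correct the error.

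The cost is rewording of hypotheses and analysis text, with no new data and no change to the primary analysis or sample size. The downside is that findings on alliance, adherence and satisfaction become associational and can no longer be presented as explaining the arm difference.

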### Procedures

Adolescents interested to take part in the study leave their email addresses on the study website [60]. They receive the participant study information by email and are asked to provide informed consent or assent (see Figure 1 for study flow). Participants younger than 14 years provide written assent, and their parent or guardian provides written consent. Participants 14 years or older provide consent on their own. Informed consents are accepted both on paper by mail and electronically as scans via email. Once the consent forms have been received, they are printed out and stored in analog form. Afterward, potential participants are screened for eligibility. Those with a score lower than 16 on the Social Phobia Inventory (SPIN) [61,62] are not included in the study but receive immediate access to the online intervention. The cutoff of 16 was chosen in reference to a previous study that showed good discrimination between healthy and subclinical adolescents [63]. Adolescents with a SPIN score of 16 or higher receive the remaining baseline questionnaires. Subsequently, they are interviewed by trained psychology graduate students via phone to ascertain whether they fulfill the diagnostic criteria for SAD or not. Those with a current diagnosis of SAD are assigned to the SAD group, while those with no current and no past SAD diagnosis are assigned to the subclinical social anxiety group. Training and weekly supervision of the graduate students are carried out by the first and last authors.

Participants are assigned to the intervention group or the control group by stratified block randomization to ensure that both groups are balanced regarding the diagnostic status: SAD or subclinical social anxiety. The randomization is carried out after all data collected by the diagnostic interview including diagnoses are entered into the electronic protocol form hosted on Qualtrics (Qualtrics XM) [64]. Randomization was set up before the start of the study by the first author (ie, number of groups, allocation ratio [1:1], and size of blocks). During the study, the allocation list was produced using an automated computer-generated random numbers table and was concealed from the investigators and the participants. After randomization, the intervention group receives immediate access to the online intervention.

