#### Sample Size

The sample size of 222 was determined in 2 a priori power analyses for the primary research question using G*Power [106] based on an intention-to-treat approach to account for possible dropouts and repeated measures ANOVA. In the SAD group, we expected a small to moderate effect size (Cohen *d*=0.35) [18,107], and for the group with subclinical anxiety, a small effect size (Cohen *d*=0.20) [38,108-110]. For both groups, we assumed an α level of 5%, power of 80%, and a correlation between measurements of *r*=0.4. Consequently, the SAD group should consist of 56 participants, and the subclinical social anxiety group of 166 participants.

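### The alliance and adherence mediation makes every path random, although the visits it names give alliance and SPIN together only twice and adherence, as tabulated, only once

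*Protocol article*

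**What the plan says.** - **Mediation Analyses.** Alliance and adherence are analysed in a 1-1-1 multilevel model "with all variables measured at assessment time points (ie, baseline, midintervention, and post intervention"), "and all causal paths allowed to vary between participants". The predictor of this model is not named.
- **Table 1, therapeutic alliance.** The scale is ticked at weeks 2, 4, 6 and 8, not at baseline. "Only adolescents in the intervention group are assessed with the WAI-I".
- **Table 1, adherence.** There is one tick, in parentheses, at week 8. The footnote explains: "Indicated time points in parentheses reflect assessments only administered in the intervention group". The same row says: "The number of finished modules, the number of completed exercises, and the time spent in the online intervention are recorded automatically".
- **Table 1, social anxiety.** The SPIN is ticked at baseline, week 4, week 8 and follow-up, not at weeks 2 or 6.
- **Procedures and Sample Size.** Allocation is 1:1 and the total is 222.

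**The concern.** A model in which all three paths differ between people needs enough repeated measurements per person to separate true differences in paths from residual noise. The occasion list under Mediation Analyses does not match the measurement schedule in Table 1, and the occasions that remain are very few. When the paths are random, the average indirect effect is a×b plus the covariance of the a and b paths, so it draws on the random-effects covariance matrix that such data support poorly. The answer on whether alliance or adherence carries the effect could then depend on starting values and software defaults.

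**Working it through.** **1. The plan's own figures.** The plan gives no sample size or power for this analysis. Its only calculation, 56 + 166 = 222, is for the primary question. It reproduces as a repeated-measures interaction with four measurements, noncentrality f²·N·m/(1−ρ), f = d/2 and ρ = 0.4: power 0.810 at N = 56 (d = 0.35) and 0.803 at N = 166 (d = 0.20). It has no bearing on the mediation except to give 222/2 = 111 in the intervention arm.

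**2. Where mediator and outcome coincide (Table 1).**

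| Occasion | SPIN | Alliance | Adherence |
|---|---|---|---|
| Baseline | yes | no | no |
| Week 2 | no | yes | no |
| Week 4 | yes | yes | not ticked, derivable from logs |
| Week 6 | no | yes | no |
| Week 8 | yes | yes | yes |
| Follow-up | yes | no | no |

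Of the three named occasions, two hold both alliance and SPIN. As tabulated, one holds both adherence and SPIN. Access to the programme starts after randomisation, so baseline use would not differ between people.

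**3. Count of random effects.** Assume the usual random intercepts (the article does not state them):

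- Mediator: M = intercept_i + a_i·X + error (2 random effects)
- SPIN: Y = intercept_i + b_i·M + c'_i·X + error (3 random effects)

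Random effects against rows for 111 adolescents:

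| Occasions | SPIN equation | Mediator equation | Both stacked |
|---|---|---|---|
| 2 | 333 vs 222 | 222 vs 222 | 555 vs 444 |
| 3 | 333 vs 333 | 222 vs 333 | 555 vs 666 |

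**4. Identification with two occasions and visit as predictor.** The mediator's 2×2 covariance matrix V holds three distinct moments. The model has four variance parameters: intercept variance, slope variance, their covariance and the residual variance. Let Z be the 2×2 invertible design matrix common to everyone. For any residual variance s below the smallest eigenvalue of V, the random-effects covariance Z⁻¹(V − sI)Z⁻ᵀ reproduces V exactly. The data cannot separate slope variance from residual variance. This is algebra and needs no assumed inputs.

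**5. Simulation.** Maximum likelihood, n = 111, no dropout. All inputs are assumptions.

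- Set A: a = b = 0.3, path SDs 0.2, intercept and residual variances 0.5, path covariance 0. True effect 0.3 × 0.3 = 0.09. 120 data sets.
- Set B: a = b = 0.3, c' = 0.2, path SDs 0.3, intercept SDs 0.6, residual SDs 0.7, correlation of a and b paths 0.3. True effect 0.09 + 0.3 × 0.3 × 0.3 = 0.117. 200 data sets.

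Singular means a smallest eigenvalue of the random-effects covariance below 0.0001.

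| Setting | A: SD of effect, random vs fixed paths | A: singular | B: mean (SD) | B: singular |
|---|---|---|---|---|
| 2 occasions, visit | 1.15 vs 0.044 | 64% | 0.165 (0.47) | 37% |
| 2 occasions, freely varying predictor | 30% wider | 97% | 0.106 (0.060) | 89% |
| 3 occasions, visit | 0.038 vs 0.025 | 93% | 0.114 (0.046) | 62% |
| 3 occasions, freely varying predictor | 30% wider | 89% | 0.113 (0.049) | 60% |

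In the first row, set A gives a ratio of 1.15/0.044, about 26. Set B gives a 5th to 95th percentile range of −0.45 to 0.92, and two starting points differed by more than 0.02 in 47% of data sets. In the other rows, set B's SD is 39% to 51% of the true effect (0.046/0.117 to 0.060/0.117).

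**The case against.** A reader might infer that the indirect effect cannot be estimated reliably under any reading of the model. The documents do not support that.

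- Random effects are integrated out, so more of them than rows does not prove non-identification. A predictor or mediator that varies between people carries information on slope variances. At three occasions the stacked model has fewer random effects than rows (5 against 6 per person).
- The severe result needs two occasions and visit as predictor, and the article names no predictor. Randomised arm cannot serve: it is a between-person variable, and the control group has neither mediator. Visit is an obvious candidate, but it remains an inference.
- The singularity rates move with the assumed inputs, and a singular fit does not by itself invalidate the average effect.
- It is tempting to blame the covariance of the a and b paths for the instability. In a smaller run of 40 data sets on set B's inputs (two occasions, visit), that covariance had an SD of 0.062 while the product a×b had 0.424, so most of the instability lay in the product.
- Nor does the single tick mean that adherence cannot be followed over time: usage is logged automatically.
- A condensed article may leave convergence fallbacks to an analysis plan that is not shown.

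All of this limits the size of the point. It does not remove it. The article states the all-random specification and the baseline occasion outright, so this is not missing detail. Nor do the alliance scores from weeks 2 and 6 rescue the model, because no SPIN is taken at those weeks and the SPIN equation gains no rows.

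**Conclusion.** The specification should be changed. For alliance, the occasion list is wrong at baseline, and the two usable occasions are too few for random a, b and c' paths: three random effects against two SPIN rows per person. If visit is the predictor, the mediator equation is not identified and the average indirect effect is in practice not estimable. With another predictor or three occasions, the cost is moderate. The effect is roughly unbiased (set B), about 30% to 50% less precise than with fixed paths (set A), and the covariance matrix is singular in about 60% to 97% of fits. For adherence, the model cannot run over time on the single tabulated value.

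The counts assume random intercepts and an even split of 222. The simulation figures rest on assumed inputs and complete data, and dropout would worsen them. This is a secondary analysis. The primary model has only a participant random effect and is unaffected.

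**What to change.** Under Mediation Analyses, for alliance and adherence only:

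1. Replace the all-random paths with random intercepts and fixed, person-mean-centred paths, and give a bootstrap or Monte Carlo interval for a×b. Allow at most one random slope, if it converges. With two occasions and visit as predictor, a slope on visit that is free to correlate with the intercept would bring back the four-parameters-from-three-moments problem.
2. Restrict the occasion list to weeks 4 and 8, where mediator and SPIN both exist.
3. Define adherence at week 4 as well as week 8 from the automatic usage logs. Without this, person-mean centring leaves nothing to analyse.
4. Name the level-1 predictor.

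Keep random paths for the ecological momentary assessment models, where three prompts a day over eight weeks give up to 3 × 7 × 8 = 168 occasions per person.

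The cost is wording only, with no new data collection. The downside is that between-person variation in these paths is not estimated, which the visit data can hardly support.

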One method of identifying mechanisms of change is to derive them theory-based and examine them as mediators [43]. Possible mechanisms of change for social anxiety may be the hypothesized maintaining factors of SAD derived from the Cognitive Model (eg, automatic thoughts, self-focused attention, safety behavior, pre-, and postevent processing [24]). In correlational and experimental studies, these factors were positively associated with a higher level of social anxiety [44-47]. However, mediation analysis inherently implies a temporal order of the relationship between the intervention, mediators, and the outcome. Therefore, these variables must be assessed longitudinally ideally at multiple times such as in ecological momentary assessment (EMA) [43,48-50]. Previous intervention studies in adolescents including EMA have mostly assessed global social anxiety, momentary social context, and affect but missed to assess individual maintaining factors [51,52]. As EMA captures events as they occur at the moment, this method thereby minimizes memory bias, incorporates contextual information from participants’ natural environment, and accounts for variability in answering behavior [43,48]. This allows to assess mediators of change and the efficacy in participants’ daily lives and extends the knowledge about intervention benefits to their natural and variable contexts [53]. Eventually, this information may add valuable input to improve interventions in the future.

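### The two exploratory EMA mediation models give the randomised condition no role, so as written they do not test whether SOPHIE works through the maintaining factors

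*Protocol article*

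**What the plan says.** The Abstract (Objective) sets out to evaluate the efficacy, moderators and mediators of the online intervention, and the Abstract (Methods) assigns mechanisms of change and daily-life generalisation to EMA. The aims at the end of the Introduction state: "we will examine if intervention effects translate into everyday life and if the postulated maintaining factors of SAD function as mediators of change". The Introduction also says what mediation requires: "mediation analysis inherently implies a temporal order of the relationship between the intervention, mediators, and the outcome".

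Under Plan of Analysis, Mediation Analyses, the article states that "Mediation effects of mechanisms of change in social anxiety will be explored in 2 different lower-level mediation analyses". It then assigns the roles:

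- **2-1-1 model:** "time will be included as a fixed effect, baseline social anxiety as a level-2 fixed effect predictor", with the mechanisms as level-1 mediator "and momentary social anxiety as a level-1 random effect outcome".
- **1-1-1 model:** "social anxiety as a random effect predictor will be assessed concurrent with the random effect mediator". The outcome, again social anxiety, is taken one prompt later, and the article calls this a lead analysis.

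Intervention condition is not predictor, covariate or moderator in either model. It is named under Main Analyses, in the model for categorical outcomes under Further Analyses, and under Network Analyses.

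**The concern.** An analysis of how a randomised treatment works needs the treatment in it. Here another variable fills the predictor slot in both models. This is therefore a stated specification that does not match the aim, rather than detail that a condensed article leaves to an analysis plan.

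As specified, the indirect effects describe how adolescents with more baseline anxiety differ in daily life (2-1-1) and how anxiety at one prompt is linked to anxiety at the next (1-1-1). Those are questions about maintenance. They are legitimate and bear on the Cognitive Model, but an intervention that never moved the maintaining factors could still produce clear indirect effects.

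The Discussion plans to use the mechanism results to show which factors matter for clinical change and to refine interventions by targeting them. If indirect effects from these models were read that way, the inference would not rest on the randomised comparison.

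**Working it through.** **1. No stated figure underlies this point.** The article's only power figures are 56 (SAD) and 166 (subclinical) under Sample Size. They reproduce as a repeated-measures ANOVA group-by-time interaction with f = d/2, m = 4 measurements, r = 0.4 and noncentrality f²·N·m/(1 − r):

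- SAD: 0.175² × 56 × 4 / 0.6 = 11.43, power 0.810.
- Subclinical: 0.10² × 166 × 4 / 0.6 = 11.07, power 0.803.

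That calculation concerns the primary question and does not involve EMA.

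**2. Roles set against the requirement.**

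| | Predictor | Mediator | Outcome | Condition |
|---|---|---|---|---|
| Introduction's requirement | intervention | mediator | outcome | is the predictor |
| 2-1-1 as written | baseline social anxiety | mechanisms | momentary social anxiety | none |
| 1-1-1 as written | social anxiety at a prompt | mechanisms, same prompt | social anxiety, next prompt | none |

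**3. Timing.** In the 1-1-1 model the predictor and mediator explicitly share a prompt, so that path has no temporal order; its mediator-to-outcome path is lagged and does. In the 2-1-1 model baseline anxiety precedes the EMA mediator, but no mediator-outcome lag is stated. Only the 1-1-1 model is called a lead analysis, and the section Ecological Momentary Assessment says the same items are asked at every prompt. Same-prompt timing in the 2-1-1 model is therefore an inference.

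**4. Available data.** Study Design says all participants receive EMA. At three prompts a day the maximum per participant is 3 × 7 × 8 = 168 over eight weeks, plus 3 × 14 = 42 after follow-up.

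**5. Illustration of the consequence.** All values here are assumed except N = 222 and 168 prompts. Let B be baseline anxiety, Z condition, t time from 0 to 1, S(t) a momentary state shared by all items at a prompt, and e, u independent noise. B, S, e and u each have variance 1.

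- Mediator: M(t) = 0.5·B − a·Z·t + S(t) + e
- Outcome: Y(t) = 0.5·B + S(t) + b·M(t − 1) + u

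Estimation used pooled or person-centred least squares rather than the planned random-effect models. The 2-1-1 model was fitted with mediator and outcome at the same prompt. Mean indirect effects over 30 runs:

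| a (treatment to M) | b (M to later Y) | 2-1-1 | 1-1-1 | condition*time to M(t) to Y(t+1) |
|---|---|---|---|---|
| 0 | 0 | 0.249 | 0.001 | 0.000 |
| 0 | 0.3 | 0.250 | 0.138 | -0.001 |
| 1 | 0.3 | 0.246 | 0.140 | -0.301 |
| 1 | 0 | 0.239 | -0.001 | 0.002 |

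Most of these follow by hand:

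- 2-1-1 with a = b = 0: the first path is 0.5. The second is var(S)/(var(S) + var(e)) = 1/2. The product is 0.25, produced by the shared state alone.
- 1-1-1 with a = 0, b = 0.3: the first path is 1/(2 + 0.3² × 2) = 1/2.18 = 0.459. The second is 0.3. The product is 0.138.
- With condition, a = 1, b = 0.3: −1 × 0.3 = −0.30.

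The 0.25 without any mediator effect depends on same-prompt timing. If the 2-1-1 model were lagged, its indirect effect would be 0.5 × b: 0 for b = 0 and 0.15 for b = 0.3, whatever the value of a. A lag thus removes the spurious part, but the model still cannot show whether treatment moves the mediator.

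**The case against.** The strongest reply is that these analyses are exploratory and that the wording of the aim, "if the postulated maintaining factors of SAD function as mediators of change", does not itself say that the change must be due to SOPHIE. Efficacy is the primary objective and is tested in a model that contains condition and its interactions. The Introduction's demand for temporal order leads to a measurement conclusion, namely repeated assessment over time, and the design provides that. An analysis plan that is not shown may add further models.

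Much of this stands. The exploratory status limits the severity, and the models have meaning as tests of the Cognitive Model. It does not remove the mismatch: the Introduction names the intervention as part of mediation, the Abstract promises mediators of the intervention, and the article itself fills the predictor slot with something else.

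Three further inferences are tempting but unsupported:

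- *The maintaining-factor models ignore temporal order throughout.* They do not. The 1-1-1 mediator-to-outcome path is lagged, and baseline anxiety precedes the EMA mediators.
- *No between-arm comparison of EMA outcomes will be made.* The article lists none, but a fuller plan may contain one.
- *An inert programme must give identical results.* This is too absolute. An intervention that changed the within-person paths would alter the 1-1-1 estimate, and the article does not say whether arms are pooled or analysed separately. The simulation pools them.

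**Conclusion.** The point holds for the two EMA mediation models as listed. They omit randomised condition and so test whether maintaining factors carry social anxiety forward, not whether SOPHIE acts through those factors. The concurrent predictor-mediator path in the 1-1-1 model is a second, smaller defect. The unstated lag in the 2-1-1 model is an ambiguity to settle.

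A reader might conclude that the trial cannot answer its mechanism question. The documents do not support that: EMA is collected in both arms, so the data can address it and only the listed models fall short.

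The size is mainly qualitative, because the effect of interest is absent from both models. The simulated figures show the direction of the problem under assumed values and simplified estimators; they do not predict this trial's results. The primary efficacy analysis and sample size are untouched. The correction should be made before the EMA analyses are run, but it is not a condition for the validity of the main result.

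**What to change.** - In the 2-1-1 model, make condition, with condition*time, the level-2 predictor and keep baseline social anxiety as a covariate.
- State the lag so that the mediator precedes the outcome, for example mediator at prompt t and outcome at prompt t+1.
- Keep the two existing models only if they are labelled as maintenance analyses that do not show how SOPHIE works. For the 1-1-1 model, say that the predictor-mediator path is concurrent and carries no direction.
- As a sensible secondary addition for the daily-life aim, specify a mixed model of momentary social anxiety on condition*time, unless the full analysis plan already has one.

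The cost is a change of wording and modest extra analysis, with no new data and no change to sample size. The Results section reports 106 participants enrolled as of April 2023, fewer than half of 222. At that stage the change could still be specified before results were known. Even with condition as predictor, the mediator itself is not randomised, so the mediator-to-outcome path remains observational and should be reported as such.
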